## Abstract

**Background:**

Despite the benefits highlighted by motor interventions based on virtual reality for children with Developmental Coordination Disorder (DCD), there are still doubts as to whether these are greater than those obtained with conventional interventions due to the absence of systematized protocols, and lack of evidence. Here, we present a protocol to systematically compare the effects of two motor-training programs (one Nintendo® Wii-based and the other no-Wii motor activities) on the motor learning in children with DCD.

**Methods/design:**

Two intervention protocols (one based on Nintendo® Wii and the other no-Wii motor activities) will be carried out, with interventions occurring twice a week in 60-min sessions, with a minimum of 12 and a maximum of 16 sessions per child.

The protocols were developed based on the domains of the Movement Assessment Battery for Children – Second Edition (MABC-2) (Manual Dexterity, Aiming and Catching, Balance), with two activities for each of the MABC − two domains. The study will include children aged 7 to 10 years with a total MABC-2 score ≤ 16, and a Developmental Coordination Disorder Questionnaire (DCDQ) score < 46 (age of 7 years), score < 55 (age group of 8 to 9 years and 11 months), or score < 57 (age of 10 years) as scored by the parents. Children will be randomly allocated by draw in one of the two intervention protocols. MABC-2 and DCDQ will be applied before and after intervention to evaluate the effects of the interventions on motor performance and parents’ perception, respectively. Motor learning will be assessed by means of the scores obtained in the games. Evaluators and therapists will be trained and evaluators will be blind regarding the data of the children in the study.

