## Methods/design

### Design and general characteristics

The protocol consists of a clinical, randomized controlled, blinded trial with two arms: training with the Wii, and conventional training without the Wii. Therapists will undergo instructional training to become familiar with all protocol activities, as well as with the scoring system of each game. The instructional training will occur a month before the beginning of the trial, which has a total duration of 8 h, for 2 h weekly. Despite the rigidly structured task settings required over the sessions, the therapists will be allowed to display their skills as therapist in order to promote a motivational environment for the children during the sessions as well as a great relationship between therapist and patient. There will be different therapists in each of the two intervention protocols, professionals from the areas of physiotherapy, physical education, and occupational therapy. The therapists in the two groups have comparable backgrounds and skill sets. All therapist teams have the same experience with pediatric rehabilitation, around 4 years of experience in this field. Children fulfilling the inclusion criteria in the study will be randomly allocated by draw into one of the two intervention groups. The flow chart of the subjects which will be allocated in the study is shown in Fig. 1 (Additional file 1).

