### Patient population

Participants will be children aged from 7 to 10 years who have been diagnosed with Development Coordination Disorder. They will be recruited from public and private elementary schools in the city of São Carlos, State of São Paulo, Brazil. The recruitment process as well as advertising of our study will be based on meetings at schools. If necessary, we will use social media to advertise the project and increase the number of potential children with DCD. Their diagnosis is based on the following *Diagnostic and Statistical Manual of Mental Disorder –V* (*DSM-V*) [5] criteria for DCD:

Criteria A – Children displaying motor performance regarded as low for the age range and for the conditions of practice opportunity. The Movement Assessment Battery for Children – Second Edition (MABC-2) will be used for the evaluation of their motor performance [26]. They will be allocated in the Amber Zone range for DCD with a total score percentage of ≤ 16, or in the Red Zone range with a total score percentage of ≤ 5, to be included in the study.

Criteria B – The limited motor performance of the children interferes significantly with daily life, school life, and leisure activities. The Developmental Coordination Disorder Questionnaire (DCDQ – Brazilian version) [27] will be used to assess, according to the perspective of the parents/caregivers, the loss in children’s functional life, in addition to direct interviews with them about the children’s routine.

Criteria C – Symptoms appeared in the initial developmental stages of the children. Direct interviews with parents/caregivers will be carried out to ascertain such characteristics.

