### Primary outcome measure

#### The primary outcomes of this study is the motor performance

##### Motor performance – MABC-2

The motor performance of the children will be assessed through the MABC-2 total standard score (TSS). As mentioned before, MABC-2 is considered a gold standard tool to identify motor performance problems in children from 3 years old. MABC-2 is divided in three different age bands: the band 1 for children aged from 3 to 6 years old; band 2 for children aged from 7 to 10 years old; and band 3 for children aged from 11 to 16 years old. There are eight tasks in total, three for the Manual Dexterity domain, two for the Aiming and Catching domain; and three for the Balance domain. Children received a specific score in each domain and their motor performance classification is based on total score and percentiles values. Children < 5° percentile present motor difficult; children < 16° percentile are at risk for motor difficult and children > 16° percentile have no motor difficult detected. According to the MABC-2 tester manual, each child spends about 30–40 min completing all tasks.

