### Randomization

Children will be randomly distributed by draw into one of the two training groups within a week at most after MABC-2 assessment. In case the draw leads to a sequence of four children in the same treatment group, the following four will be automatically allocated in the other. Once the distribution of blocks of four children is equalized, a new draw will be done for the following children to be randomly distributed. A person not involved with the study will receive a list of all children and will write in one piece of paper the term “Wii” and in another piece of paper the term “no-Wii.” This person will fold each piece of paper and will request to another collaborator not involved in this study to choose between the two papers. Then, following this draw, each child will be allocated into Wii or the no-Wii intervention group.

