### Statistical methods

At first, descriptive analysis will be done with the distribution of relative and absolute frequencies, averages, standard deviations, medians, mode, and minimum and maximum number in order to characterize children. All data will be inserted into spreadsheets in the SPSS statistical package, version 20.0 for Windows.

Next, analyses regarding normality and homogeneity tests will be performed. There will be two independent groups because of the design of the study, and there will also be intergroup comparative analyses in each one, constituting the results of motor performance and learning evaluation pre test and post test, as well as the comparisons between such intergroup evaluations.

In case of parametric distribution, analyses will be performed through analysis of variance (ANOVA) and analysis of co-variance (ANCOVA) utilizing the Bonferroni correction.

In case of non-parametric distribution, intergroup comparative analyses will be carried out by means of the Mann-Whitney *U* test and intergroup comparison through the Wilcoxon test. The significance level adopted will be *p* < 0.05 for all measurements. In order to verify the dimension of the effect of the interventions realized, the Cohen test will be applied with the following reference values: *d* = 0.3 indicates a small dimension of the effect, while *d* = 0.5 and *d* = 0.8 indicate a moderate and a large one [30], respectively.

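### A single arm's pre-post gain cannot show that an intervention works, because children are selected for low scores on the outcome tests and no arm is untreated; inference should rest on the between-arm contrast

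*Protocol article*

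**What the plan says.** **Entry.** On the MABC-2, Patient population says: "They will be allocated in the Amber Zone range for DCD with a total score percentage of ≤ 16". The lower Red Zone (5 or below) also qualifies. The Abstract adds age-specific parent-questionnaire cut-offs: "Developmental Coordination Disorder Questionnaire (DCDQ) score < 46 (age of 7 years), score < 55", with a third limit at age 10.

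**Outcomes.** The same instruments measure the result. The Abstract states: "MABC-2 and DCDQ will be applied before and after intervention to evaluate the effects of the interventions on motor performance". For the primary outcome, "The motor performance of the children will be assessed through the MABC-2 total standard score (TSS"). The DCDQ is a secondary outcome, completed before and after treatment.

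**Arms and timing.** The trial has "two arms: training with the Wii, and conventional training without the Wii". The draw takes place "within a week at most after MABC-2 assessment". The text describes no second MABC-2 between selection and the start of treatment.

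**Analysis.** Sample size rests on the Wii arm's within-group MABC change: 58.0 (SD 8.7) to 65.5 (SD 9.9) in a pilot of 6, effect size 0.80, 80% power, alpha 5%. This gives 15 per group, raised to 16. Statistical methods plans analyses "constituting the results of motor performance and learning evaluation pre test and post test", together with comparisons between groups. The parametric route is ANOVA and ANCOVA. The non-parametric route is Mann-Whitney and Wilcoxon, both labelled as intergroup; since Mann-Whitney compares the arms, Wilcoxon reads as the paired pre-post test. The section adds: "In order to verify the dimension of the effect of the interventions realized, the Cohen test will be applied". It does not say whether that d is computed within or between arms.

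**The concern.** Children chosen because one measurement was low will on average score higher when measured again, even if nothing is done. Taking the same test a second time can add a practice gain. With no untreated arm, neither can be separated from an intervention effect in an arm's own change. Yet that change is the only quantity the trial is sized to detect, and nothing in the text warns against reading it as efficacy. At stake is a conclusion that Wii training, or no-Wii training, improves motor performance when some or all of the gain comes from selection. The argument covers the MABC-2 and DCDQ. It does not cover the game scores, on which children are not selected.

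**Working it through.** **1. Reproduce the plan's figure.** Effect size from the pilot: 7.5 / √((8.7² + 9.9²)/2) = 7.5 / 9.32 = 0.805, stated as 0.80. A two-sided 5% paired t-test with standardised mean change dz = 0.80 needs n = 15 for 80% power (power 0.82 at 15, 0.85 at 16). The stated 15 is therefore the size for a within-arm pre-post test.

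**2. Regression to the mean with no intervention effect.**

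From the documents: selection at or below the 16th percentile, and 16 per arm.

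Assumed: pre and post scores bivariate normal with unit SD; the selecting score serves as the pre-test; test-retest correlation r in the unselected population from 0.70 to 0.95. The protocol gives no value for r.

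Formulas, with c = −0.994 and λ = φ(c)/Φ(c) = 0.243/0.16 = 1.52:
- Variance of the selected pre-score: v = 1 − cλ − λ² = 0.20.
- Mean change: (1 − r)λ.
- SD of change: √((1 − r)²v + 1 − r²).
- dz = mean change / SD of change.
- Rejection rate: two-sided noncentral t, 15 df, noncentrality dz√16.

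Worked case, r = 0.80: mean change 0.20 × 1.52 = 0.304; SD √(0.04 × 0.20 + 0.36) = 0.607; dz = 0.50.

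| r | mean change (population SD) | dz | arm significant | at least one of two arms significant |
|---|---|---|---|---|
| 0.70 | 0.456 | 0.63 | 65% | 88% |
| 0.80 | 0.304 | 0.50 | 47% | 72% |
| 0.90 | 0.152 | 0.35 | 25% | 45% |
| 0.95 | 0.076 | 0.24 | 15% | 28% |

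The last column is simulated (40,000 trials); simulation also agrees with the per-arm rates to within one percentage point. The artefact is 30% (0.24/0.80) to 78% (0.63/0.80) of the planning effect size.

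**3. Allow for a second selection measure.** Entry also needs a low DCDQ and interview-based criteria, which favours children whose true ability is low and so reduces the artefact. Assume a second measure, also cut at its 16th percentile and correlated 0.4 to 0.6 with true ability. By simulation the per-arm rate falls to about 39-46% (r = 0.70), 26-31% (r = 0.80) and 14-17% (r = 0.90).

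**4. Sensitivity the other way.** If every child were at or below the 5th percentile, with the MABC-2 alone selecting, the per-arm rates would be 89%, 72%, 42% and 23% for the four values of r.

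**5. The randomised contrast.** In the simulations of steps 2 and 4, the between-arm test of change rejects in 4.8% to 5.1% of trials, because the artefact is equal in expectation in both arms. Its power is a separate matter. With 16 per arm, an unadjusted two-sample t-test has 59% power at a between-arm d of 0.80. It would need 26 per arm for 80%.

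**The case against.** The strongest reply is that the stated aim is comparative throughout. The Abstract sentence on before-and-after testing follows directly on random allocation and does not say within-arm, so it fits a baseline-adjusted comparison between arms equally well. Between-arm tests, including ANCOVA, are already planned. This stands, and it limits the point to single-arm efficacy statements. It does not remove the point, because the sample size rests on the within-arm change alone and pre-post tests are planned.

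Two stronger readings are tempting, and the text supports neither.
- A reader might infer that Cohen's d will be computed on each arm's pre-post change. Statistical methods leaves this open; the defect is that it is unspecified.
- A reader might infer that a significant result in one arm and not in the other will be taken as a difference between the arms. No sentence proposes this, and direct between-arm tests are planned.

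Two objections to the size also stand. The section on anthropometric measurements mentions an MABC-2 pre-test evaluation, and the figure describing the screening and assessment phases is not shown. A separate pre-test after screening cannot be excluded, and it would shrink the bias. And selection on the MABC-2 alone overstates the artefact when other criteria also select, which step 3 of the working addresses.

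It can also be said that the choice of confirmatory result belongs in an analysis plan that is not shown. But the protocol itself fixes the within-arm change as the basis of its sample size.

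**Conclusion.** The point holds for claims that either arm is effective on its own. Under the stated assumptions, a within-arm paired test with no intervention effect would be significant in about 65% to 15% of arms for r from 0.70 to 0.95 with selection on the MABC-2 alone. With a second, correlated selection measure the range is about 39-46% (r = 0.70) to 14-17% (r = 0.90). Both lie well above the nominal 5%. These figures illustrate the mechanism and are not estimates for this trial. They depend on an assumed correlation, on normality, on reading the entry limit as the 16th percentile, and on the selecting score serving as the pre-test. The DCDQ was not modelled as an outcome, though its entry cut-offs bring in the same mechanism. Retest practice was not quantified and would add to the gain.

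The documents do not support the inference that the comparison of Wii with no-Wii is biased: regression to the mean affects both randomised arms alike.

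**What to change.** - **Statistical methods:** make the between-arm difference in post-test MABC-2 total standard score, and likewise in DCDQ, the basis for inference. Estimate it by ANCOVA with the baseline score as covariate, and compute Cohen's d on this contrast.
- **Statistical methods:** report within-arm changes descriptively. State that they cannot be attributed to the intervention, because of selection on the same instruments and the lack of an untreated arm. Correct the label of the Wilcoxon comparison.
- **Sample size:** state that the 80% power applies only to the within-arm change and not to the between-arm comparison.

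This needs no new data or visits, and ANCOVA is already named in the plan. The cost is that single-arm efficacy claims are given up, and that the limited power of the comparison between arms becomes explicit.

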**Discussion:**

Owing to its motivating aspects, training with Nintendo® Wii may be particularly beneficial for children with DCD. The results of this study protocol should help researchers and therapists to better understand the benefits of Nintendo® Wii-based motor intervention over those obtained with no-Wii interventions in children with DCD. It should also create references about more systematized protocols for replication in clinical practice, seeking the improvement of the motor components of these children.

**Trial registration:**

RBR-89ydgj

## Background

Children with compromised motor control are widely mentioned in various studies [1–3], due to the fact that affected motor ability directly or indirectly affects the performance of functional activities. Developmental Coordination Disorder (DCD) has a number of characteristics related to motor development that have a meaningful impact on the daily and school life of many children [4]. DCD diagnostic criteria involve significant motor alterations, compromising daily life, school life or leisure activities, and the fact that these alterations appeared in the earlier stages of children’s life despite sufficient practice of motor activities [5].

Neuroimaging data have highlighted important cortical alterations in children with DCD, specifically in the frontal, parietal, and temporal regions [6, 7] during the performance of manual tasks, which may be associated with a slower processing of motor information in these children when compared to typical ones [8].

Such restrictions may lead to reduced social participation [9] and school performance [10] meaningfully, since many children with DCD tend to isolate themselves from other children because they cannot perform motor activities at the same pace as their peers due to the limitation in information processing. They also tend to become more anxious and insecure [11], and feel more motivated to perform activities when they are alone, as well as those with sedentary characteristics [12].

Motivating strategies in the intervention with these children seem to be the key to success in terms of participation and functional gains [13]. The use of technology has gained prominence in recent years among the strategies adopted since resources, such as interactive games based on virtual reality (VR), offer instant feedback and a larger number of repetitions of body movements per session than many conventional motor intervention techniques, such as physiotherapy, occupational therapy, cognitive orientation to daily occupational performance (CO-OP) or Neuromotor Task Training (NTT) [14]. This facet may promote greater efficacy of the motor intervention in these children.

More specifically, the use of the Nintendo® Wii in the rehabilitation of children with motor alterations has been promoted for ease of measuring the force applied and capturing pressure change available in the Wii Balance Board (WBB), besides the fact that the Wii motion control allows great stimulation of the hand-dexterity motor component [15, 16]. Balance, Aiming and Catching are the domains of the Movement Assessment Battery for Children (MABC), that are regarded as the gold standard for the identification of DCD in children [17]. These aspects make the Nintendo® Wii very useful as a VR resource for motor interventions in children with DCD.

At present, however, little evidence exists in the literature on comparisons between the benefits of VR training, such as Nintendo® Wii, and conventional interventions such as without Wii [18–20].

The handful of existing studies that compare interventions with and without VR for children with DCD still show limitations about evidence created by the VR intervention [19, 21–24]. Moreover, it is not clear whether one type of intervention offers greater gains than the other due to the shortcomings from the scarce previous studies already published. Based on a recent systematic review by Hickman et al. [25] evidence for advantages gained by a VR intervention for children with DCD are not consistent in relation to conventional therapy. The authors argued that due the heterogeneity of assessment tools and outcomes fair comparisons were not possible. So, we believe that in this study we might see fair comparisons because the tasks will be closely matched by motor domain target into the training protocol.

These limitations of present approaches hinder a well-informed conclusion as to whether training with VR is more effective than conventional training in children with DCD. In this paper we present a protocol for a randomized clinical trial to systematically compare two motor-training programs (with and without Nintendo® Wii) on motor learning in children with DCD.

## Methods/design

### Design and general characteristics

The protocol consists of a clinical, randomized controlled, blinded trial with two arms: training with the Wii, and conventional training without the Wii. Therapists will undergo instructional training to become familiar with all protocol activities, as well as with the scoring system of each game. The instructional training will occur a month before the beginning of the trial, which has a total duration of 8 h, for 2 h weekly. Despite the rigidly structured task settings required over the sessions, the therapists will be allowed to display their skills as therapist in order to promote a motivational environment for the children during the sessions as well as a great relationship between therapist and patient. There will be different therapists in each of the two intervention protocols, professionals from the areas of physiotherapy, physical education, and occupational therapy. The therapists in the two groups have comparable backgrounds and skill sets. All therapist teams have the same experience with pediatric rehabilitation, around 4 years of experience in this field. Children fulfilling the inclusion criteria in the study will be randomly allocated by draw into one of the two intervention groups. The flow chart of the subjects which will be allocated in the study is shown in Fig. 1 (Additional file 1).

**Fig. 1 Fig1:**
[figure not shown]
Flow chart of participant inclusion

### Patient population

Participants will be children aged from 7 to 10 years who have been diagnosed with Development Coordination Disorder. They will be recruited from public and private elementary schools in the city of São Carlos, State of São Paulo, Brazil. The recruitment process as well as advertising of our study will be based on meetings at schools. If necessary, we will use social media to advertise the project and increase the number of potential children with DCD. Their diagnosis is based on the following *Diagnostic and Statistical Manual of Mental Disorder –V* (*DSM-V*) [5] criteria for DCD:

Criteria A – Children displaying motor performance regarded as low for the age range and for the conditions of practice opportunity. The Movement Assessment Battery for Children – Second Edition (MABC-2) will be used for the evaluation of their motor performance [26]. They will be allocated in the Amber Zone range for DCD with a total score percentage of ≤ 16, or in the Red Zone range with a total score percentage of ≤ 5, to be included in the study.

Criteria B – The limited motor performance of the children interferes significantly with daily life, school life, and leisure activities. The Developmental Coordination Disorder Questionnaire (DCDQ – Brazilian version) [27] will be used to assess, according to the perspective of the parents/caregivers, the loss in children’s functional life, in addition to direct interviews with them about the children’s routine.

Criteria C – Symptoms appeared in the initial developmental stages of the children. Direct interviews with parents/caregivers will be carried out to ascertain such characteristics.

Criteria D – The motor limitations showed by the children do not come from intellectual or visual impairment, or neurologic conditions such as cerebral palsy, dystrophy or any degenerative disease. In order to eliminate these associated conditions, school data about the children will be assessed, teachers will be interviewed and also physiotherapists will offer assessments in order to eliminate any sign of the mentioned neurologic conditions. In addition, psychiatric disorder history will be assessed through the parents’ interview as well as based on children’s forms at school in order to avoid the heterogeneous profile of those children. If we find children who have already received a psychiatric diagnosis (other than DCD) we will exclude them from the study. In addition, we will exclude children who may have undiagnosed psychiatric conditions but have recognizable contra-indications such as high levels of anxiety, impulsivity or attentional difficulties.

Highly anxious, inattentive or oppositional children who might be unable to complete either intervention program will be excluded from the study because they might find the interventions distressing. Children will be allowed to continue regular physical education classes at schools. Other concomitant care or interventions during the period of intervention will not be allowed.

In case any children are missed before the intervention ends, we use the intention-to-treat analysis.

